#### Cognitive training with computerised exercises (an experimental intervention group, CogniFit)

The supposed mechanism of CogniFit is derived from evidence that computerised exercises focusing on auditory and verbal processing are likely to yield improved verbal learning and memory [12], and activate the brain reward system that drives brain plasticity in adults with schizophrenia [40, 41]. Exercises include the elements needed for an effective cognitive intervention: a large number of specific repetitive learning trials driven by maximally enduring, neurologically reliable cognitive gains, and individually adapted content based on each learner’s needs [12]. To match the training regimen for each participant’s unique cognitive needs (deficits), a short assessment using CogniFit exercises will be done at the beginning of the intervention. During each training session, the participants will be instructed to play memory games and at least one exercise from each of the three categories: memory, spatial perception, and mental planning. Otherwise, they will be free to choose which exercises they wish to play.

During the first gaming session, a game will be introduced to the participant, and its use will be tested together with an RA. The participant’s ability to play digital games will be explored to ensure that they have the basic gaming skills required for active gaming (how to start the computer, how to play the game, how to change game options, and so on). During each gaming session, an RA will be available for gaming support. The RA will also provide assistance, if required, based on each gamer’s individual needs.

#### Entertainment video gaming (an active control group)

The video game offers entertainment without any known cognitive or health-related outcome. We will use SIMS 4, which includes a variety of personalities portrayed as cartoon characters that be customised based on gamers’ needs and wishes. For example, a gamer can change the clothing of characters, develop their stories, build homes, have the characters travel and build relationships between characters. As in the intervention group, an RA will be available during each gaming session to guide and support gaming skills and initiatives.

#### Treatment as usual (a passive control group)

No specific gaming intervention will be offered to those who receive treatment as usual. To minimise the risk of intervention contamination, the participants will be encouraged not to play video games during the study period and will be asked to report any video gaming with which they may have engaged.

### Outcome evaluation (primary and secondary outcomes)

#### Primary outcome

Verbal working memory will be measured with the Letter-Number-Sequencing task (Letter-Number-Span-Test, LNST) from WMS III (Wechsler Memory Scale, the 3rd Edition, simplified/traditional Chinese versions). The instrument includes an NIMH-MATRICS (US National of Institute of Mental Health, the Measurement and Treatment Research to Improve Cognition in Schizophrenia) battery [42].

#### Secondary outcomes

##### Cognitive functioning

A battery of cognitive tests will be used to measure the processing speed [Trail Making Test, TMT, A [42]], attention and vigilance [Sustained Attention to Response Task, SART], visuospatial working memory [Spatial Span from WMS III [42]], and reasoning and problem solving [Wisconsin Card Sorting Test [42]]. The instruments to be used are well tested, reliable, recommended, and available in simplified/traditional Chinese, either in paper or digital format [42].

##### Social functioning

A Chinese version of the Brief Social Phobia Scale, BSPS, will be used for assessing the severity of and treatment response to social phobia [43]. The Cronbach’s alpha for the Chinese version is 0.88, which states a high level of internal consistency [43].

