**Methods:**

The participants will be recruited from different outpatient units (e.g., outpatient psychiatric units, day hospitals, residential care homes). The controlled clinical trial will follow a three-arm parallel-group design: 1) cognitive training (experimental group, CogniFit), 2) entertainment gaming (active control group, SIMS 4), and 3) treatment as usual. The primary outcomes are working memory function at 3-month and 6-month follow-ups. The secondary outcomes are patients’ other cognitive and social functioning, the ability to experience pleasure, self-efficacy, and negative symptoms at 3-month and 6-month follow-ups. We will also test the effectiveness of gaming interventions on neurocognitive outcomes (EEG and 3 T MRI plus rs-fMRI) at a 3-month follow-up as an additional secondary outcome. Data will be collected in outpatient psychiatric services in Hong Kong. Participants will have a formal diagnosis of schizophrenia and be between 18 and 60 years old. We aim to have a total of 234 participants, randomly allocated to the three arms. A sub-sample of patients (*N* = 150) will be recruited to undergo an EEG. For neuroimaging assessment, patients will be randomly allocated to a subset of patients (*N*=126). We will estimate the efficacy of the interventions on the primary and secondary outcomes based on the intention-to-treat principle. Behavioural and EEG data will be analysed separately.

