## Methods

### Objectives

This study aims to compare the effectiveness of cognitive training using computerized gaming exercises to that of entertainment video gaming and a non-gaming, passive control group, looking at a range of outcomes. The primary objective is to test the effects of the interventions on patients’ cognition, especially on working memory at 3-month and 6-month follow-ups. The secondary objectives are to test the effects of the interventions on patients’ other cognitive and social functioning, the ability to experience pleasure, self-efficacy, and negative symptoms at 3-month and 6-month follow-ups. Additional secondary outcomes are EEG brain activity and structure related to working memory function at a 3-month follow-up.

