### The hypotheses

Primary hypothesis:
Cognitive training with computerised exercises is more effective than entertainment video gaming or the non-gaming control in improving patients’ working memory at a 3-month and/or 6-month follow-up.

Secondary hypotheses:
2.Cognitive training with computerised exercises is more effective than entertainment video gaming and the non-gaming control in improving patients’ cognitive and social functioning, experience of pleasure, and self-efficacy at a 3-month and/or 6-month follow-up.3.Cognitive training with computerised exercises is more effective than entertainment video gaming and the non-gaming control in improving negative symptoms in schizophrenia at a 3-month and/or 6-month follow-up.4.Cognitive training with computerised exercises is more effective than entertainment video gaming and the non-gaming control in improving neurocognitive outcomes (EEG signals, brain activity and structure) at a 3-month follow-up.

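### The secondary outcome of social functioning is worded more broadly than its only assigned instrument, a social phobia scale, supports

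*Protocol article*

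**What the plan says.** Social functioning runs through the protocol article as an efficacy outcome.

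- Abstract, Methods: "The secondary outcomes are patients’ other cognitive and social functioning", followed by the other clinical domains.
- Objectives: "The secondary objectives are to test the effects of the interventions on patients’ other cognitive and social functioning", again with the other domains, at 3 and 6 months.
- The hypotheses, secondary hypothesis 2: cognitive training is expected to be superior to both comparators in "improving patients’ cognitive and social functioning, experience of pleasure, and self-efficacy at a 3-month and/or 6-month follow-up".
- Data collection and follow-up: social functioning is listed among the outcomes collected at baseline, 3 months and 6 months.
- Data analysis, Cognitive and clinical outcomes: it is listed among the secondary outcomes that each get a separate multilevel model of the same form as the primary model.

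The measurement is set out under Secondary outcomes, in the paragraph headed Social functioning. One instrument is named, "A Chinese version of the Brief Social Phobia Scale, BSPS", and the same sentence says that it "will be used for assessing the severity of and treatment response to social phobia". The only measurement property given is internal consistency: "The Cronbach’s alpha for the Chinese version is 0.88, which states a high level of internal consistency".

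**The concern.** The heading of the outcome paragraph names one construct and the sentence beneath it describes another. Severity of social phobia and social functioning may be related, but the article does not say that one stands for the other. If the BSPS result is read under the heading and hypothesis as now worded, a lower phobia score could be taken as better social functioning, and a null result as no effect on it. Neither follows from a scale that the article describes only as a measure of social phobia. The label matters because the abstract's background presents social impairment as a target of gaming, and the Discussion expects the findings to inform recommendations to patients and decision makers.

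**Working it through.** No arithmetic applies. The point depends on no error rate, effect size, variance or sample size. The check was to follow the construct from objective to instrument, and then to see whether any other instrument fills the gap.

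**Step 1. Instruments in Table 1 and the domain the text gives each.**

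| Instrument | When measured | Domain assigned in the text |
|---|---|---|
| LNST | baseline, 3, 6 months | verbal working memory (primary) |
| TMT, SART, Spatial Span, Wisconsin Card Sorting | baseline, 3, 6 months | other cognitive functioning |
| BSPS | baseline, 3, 6 months | headed social functioning; described as social phobia |
| TEPS | baseline, 3, 6 months | experience of pleasure |
| GSE | baseline, 3, 6 months | self-efficacy |
| CAINS | baseline, 3, 6 months | negative symptoms |
| EEG, MRI | baseline, 3 months | neurocognition |
| CDS-C, SAS, BARS, AIMS, MMSE, IQ, medication dose, computer use, background | preparatory phase only | depression, movement scales, screening and background |
| ACP | allocation | none given; footnoted as discontinued |

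Instruments assigned to social functioning: 1 (BSPS). Instruments that the text describes as measuring social functioning: 0.

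**Step 2. Could another instrument carry the claim?** CAINS is the nearest candidate, but the protocol gives it to negative symptoms, which has its own hypothesis (number 3). The depression and movement scales are collected once, before allocation, so they cannot show change. Nothing else is offered.

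**Step 3. Is social phobia itself an objective?** It appears in the Social functioning paragraph, in Table 1 and in the abbreviation list. It is in no objective or hypothesis, and it is neither an inclusion nor an exclusion criterion. The Background speaks of social relationships and social interaction, not phobic symptoms.

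**Step 4. Does the stated psychometric support close the gap?** A Cronbach's alpha of 0.88 says that the items agree with one another. It does not say which construct they measure, so it cannot turn a phobia score into a functioning score.

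**Step 5. How far does it reach?** The secondary objectives list five clinical domains: other cognition, social functioning, pleasure, self-efficacy and negative symptoms. One of the five is affected. The sample size is built on verbal working memory and does not use the BSPS.

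**The case against.** Four points can fairly be made on the other side.

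*The item content is not shown.* A reader might infer that the trial has no measurement of social functioning at all. The documents do not support that. Neither the BSPS items nor the CAINS items are reproduced, so nobody can tell from the article how far either one touches on functioning. This objection stands: what can be said is that no other instrument is assigned to the domain.

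*The article is open about the instrument.* The scale is named in the outcome paragraph and in Table 1, and its construct is stated, so a careful reader of the results can see what was measured. A reader might also infer that the trial's conclusion will be wrong whichever way the result falls. The article contains no reporting text for this outcome, so that is a risk of over-reading and not a demonstrated error. This also stands, but it does not remove the mismatch, because hypothesis 2 and the objective are what the result will be set against.

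*A fuller protocol may justify the scale as a proxy.* It may, and the absence of a rationale from a journal article is not held against the plan here. The point rests on what the article does state: a domain heading and hypothesis of one kind, and a measure described as being of another.

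*Renaming is not free.* The trial is registered and the Study status section says that recruitment is ongoing. Changing the name of a secondary outcome part-way is an outcome change that has to be documented. This stands and is reflected in the fix.

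**Conclusion.** The concern holds in a narrow form. The wording of one element of the secondary objective and of hypothesis 2 is broader than the construct that the article itself assigns to the BSPS, and no other instrument is assigned to make up the difference. A BSPS result supports a conclusion on social phobia severity and none on social functioning in general.

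A reader might take this to mean that the trial cannot support its main claim. It does not: the primary hypothesis concerns working memory, and the primary outcome, the sample size and the other secondary outcomes are untouched. Nor does it help to multiply the problem by the number of group-by-time contrasts in the model for this outcome; it is one labelling problem, whatever the number of contrasts.

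The conclusion assumes that the article's description of the BSPS is the intended one and that no other document assigns a further social functioning measure. It should be corrected, but it is a matter of secondary-outcome validity and does not threaten the trial.

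**What to change.** Before outcome data are analysed, issue a dated and explained amendment, and bring the registry record into line with it (the record was not available here, so its current wording needs checking). In that amendment:

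1. Name the outcome social phobia (social anxiety) symptom severity measured by the BSPS in the abstract, the objectives, hypothesis 2, the Social functioning paragraph, and the data collection and analysis text. A lighter alternative is to keep the domain heading and state in those places that it is operationalised solely as BSPS social phobia severity.
2. State that conclusions from this outcome are limited to that construct, and that none is drawn on social functioning in general.

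No new instrument, visit or analysis is needed; the planned multilevel model runs unchanged on the same score. Adding a dedicated functioning scale now is less workable, because participants already enrolled would have no baseline value. The cost is a documented mid-trial relabelling, which is why the date and the reason should be on record before results are seen, and the loss of the broader social functioning claim.

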##### Experience of pleasure

The Temporal Experience of Pleasure Scale (TEPS, Chinese version) covers anticipatory and consummatory components (Cronbach’s alpha=0.83; test-retest reliability r=0.79) [44].

##### Self-efficacy

The Chinese version of the General Self-Efficacy Scale, GSE, a self-reporting measurement of self-efficacy with good internal consistency (Cronbach’s alpha = 0.91), will be used [45].

##### Negative symptoms of schizophrenia

The Chinese version of the Clinical Assessment Interview for Negative Symptoms (CAINS) [46] will be administered by qualified psychiatrists who have received proper training for this assessment tool. The item-total score correlation will also be presented for each item, and can range from 0.58 to 0.81. The internal consistency (Cronbach’s alpha) for the scale is high (0.91) [46].

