### Randomisation, allocation concealment and blinding (masking)

After baseline data collection, the trial manager will be notified of new participants. Each participant will be allocated to one of the three arms based on a list of computer-generated random numbers provided by an external clinical trial randomisation service (blocks of 6 consecutive patients, a 1:1:1 ratio). Allocation will be masked to the trial statistician, but it cannot be masked to the research assistants (RAs) who will supervise the gaming sessions and collect follow-up outcome data, or from the study unit staff who will work with the patients. Furthermore, a sub-sample of 150 participants will be recruited for EEG analysis, and 126 participants from our total sample will be randomly selected and assigned to neuroimaging assessment at baseline (fMRI). Again, the participants for neuroimaging assessment will be allocated based on a separate list of computer-generated random numbers provided by an external clinical trial randomisation service (blocks of 6 consecutive patients, a 1:1:1 ratio). The trial manager will inform the RAs the identities of participants allocated to fMRI assessment.

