### Data collection and follow-up

To avoid burdening the patients, data will be collected in separate phases (see Table 1):
A preparatory data collection (estimated 45 min) will be collected only once, at the beginning of the study. It aims to collate the background information of the participants to determine their capacity for informed consent and any other potential factors that might restrict participation in the intervention (background information, IQ, medication dosage [based on medical records], MMSE, CDS-C, SAS, BARS, AIMS).2)For the primary (verbal working memory) and secondary outcomes (estimated 75 min) (cognitive and social functioning, experience of pleasure, self-efficacy, negative symptoms), the data will be collected at three points in time: at baseline, after the intervention (3-month follow up) and at a six-month follow-up (6 months after baseline).3)The EEG measures taken during the working memory test will be collected at baseline and 3 months after baseline only (EEG 1 h; rsfMRI and structural MRI, 45 min).

**Table 1 Tab1:** Instruments and study stages

TIME POINTS Instruments	Eligibility screening	Preparatory data	Baseline	Allocation	Intervention	3 month follow-up	6 month follow-up
Inclusion/exclusion criteria	**X**						
Background information		**X**					
IQ (from medical records if available)		**X**					
Current medication dosage		**X**					
Computer use		**X**					
MMSE		**X**					
Calgary Depression Scale for Schizophrenia, CDS-C		**X**					
Simpson-Angus Rating Scale, SAS		**X**					
Barnes Akathisia Rating Scale, BARS		**X**					
Abnormal Movement Involuntary Scale, AIMS		**X**					

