**Study groups**							
Cognitive training with computerized exercises (experiment group)					X		
Entertainment video gaming (active control group)					X		
TAU (passive control group)							

^a^Convenience sample; ^b^Randomised subsample; ^c^ACP test planned but need to discontinue due to technological problems of the measure

First, for the primary and secondary outcomes (cognitive and social functioning, experience of pleasure, self-efficacy, negative symptoms), the data will be collected in paper format or digital format [5] by a trained psychologist or RA.

Second, the EEG will be recorded during resting state and a multi-objects visual working memory task (VWM). The task, modified from our prior studies [52], will be performed so that the neuronal mechanisms limiting VWM performance and capacity can be identified during the memory retention period. Subjects will attend either hemifield, depending on the pre-stimulus cue, and memorise a visual display containing one to six objects. After the retention period, a second stimulus will appear, and the subject will answer whether the stimulus presented in the second display matches part of the first display or not. We will correlate both local and large-scale neuronal dynamics with the task performance, both in pre-training and post-training neuroimaging sessions.

Third, fMRI scans will be acquired using a Philips 3 T MRI scanner. During scanning, a painless procedure, patients will rest on a table, which will be slid into a large tunnel-shaped scanner. As there will be a constant drumming noise during scanning, earplugs or earphones will be provided. During the examination, the patient will be able to freely communicate with staff via an intercom. Resting-state fMRI data will be acquired using T2-weighted echo planar pulse sequence imaging (300 whole-brain volumes were collected with slice thickness=4 mm, TE=30 ms, TR= 2000 ms, flip angle=90 degrees, spatial resolution 3x3x4 mm isotropic voxels, transverse orientation, 32 slices fully covering the cerebral cortex and the cerebellum, acquisition time = 10 min). Structural MRIs will be acquired with the MP-RAGE T1 sequence. A DTI of the axonal tracts in cerebral white matter will be performed with a protocol validated in the Human Connectome Project. We will acquire a 15-min session of resting-state data to obtain high-quality measurements of intrinsic functional connectivity of BOLD signals (fMRI) [53] and critical dynamics (fMRI) [54].

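### The protocol gives conflicting rules on who rates negative symptoms (CAINS), so unmasked research assistants who supervise the gaming may rate the scale behind hypothesis 3 at follow-up

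*Protocol article*

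**What the plan says.** Three sections of the protocol article bear on who rates CAINS.

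- **Secondary outcomes, Negative symptoms of schizophrenia:** CAINS "will be administered by qualified psychiatrists who have received proper training for this assessment tool".
- **Data collection and follow-up, text after Table 1:** the rule opens with "First, for the primary and secondary outcomes (cognitive and social functioning, experience of pleasure, self-efficacy, negative symptoms" and goes on to say that "the data will be collected in paper format or digital format [5] by a trained psychologist or RA". No psychiatrist is mentioned.
- **Randomisation, allocation concealment and blinding:** the statistician is the only role stated to be masked. Of allocation the section says that "it cannot be masked to the research assistants (RAs) who will supervise the gaming sessions and collect follow-up outcome data". Unit staff who work with the patients are also said to be unmaskable. CAINS is not excepted.

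Two further places show what depends on the answer. Hypothesis 3 claims superiority of cognitive training over both comparators "in improving negative symptoms in schizophrenia at a 3-month and/or 6-month follow-up". For the primary and secondary outcomes, "the data will be collected at three points in time: at baseline, after the intervention (3-month follow up) and at a six-month follow-up". Table 1 marks CAINS at those three visits and lists no other measure of negative symptoms.

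**The concern.** CAINS is an interview, and the score depends on the interviewer's judgement. The outcome section describes a trained psychiatrist with no stated part in the gaming. The other two sections, read together, allow a rater who knows the arm and has sat with the participant through a programme of 60 planned sessions. These are materially different ways of measuring the same outcome. A reader of the results could not tell from the protocol which one was used.

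Two things are at stake for hypothesis 3. One is rating by someone who knows the allocation, which can colour a judgement-based score. The other is a change in the type of rater between baseline and follow-up, which goes straight into the change scores being compared.

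**Working it through.** No figure in the protocol depends on this point, so the check is a comparison of the texts, followed by a symbolic look at the consequence.

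**1. Can the statements be reconciled as rule and exception?** The data-collection sentence might be a general rule with CAINS as a silent exception. That reading fails because the sentence lists negative symptoms by name and CAINS is the only instrument for them.

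**2. Does collecting mean only handling the forms?** The same sentence covers the cognitive tests, which the psychologist or RA would have to administer. Nothing in it separates interviewing from paperwork for CAINS.

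**3. Which rater applies at which visit?**

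| Section | Rater | Visits | Masking of that rater |
|---|---|---|---|
| Negative symptoms | Trained psychiatrist | Not limited | Not stated |
| Data collection | Psychologist or RA | Not limited | RA: unmasked; psychologist: not stated |
| Randomisation and blinding | RA | Follow-up | Unmasked |

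Only the last row is tied to particular visits. Set beside the first row, it permits a psychiatrist at baseline and an RA at 3 and 6 months. No section requires the same type of rater throughout.

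**4. When could knowledge of the arm enter?** Randomisation follows baseline data collection, so baseline ratings precede allocation. Knowledge of the arm can affect only the follow-up ratings, which are the ones the blinding section gives to RAs.

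**5. What would a change of rater do to the analysis?** The planned model tests group-by-time interactions. Let d be the mean difference between RA and psychiatrist ratings of the same patient, and p_k the share of follow-up ratings in arm k made by RAs, with baseline ratings made alike in all arms.

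- Bias in the contrast of arms j and k = d × (p_j − p_k).
- If p_j = p_k, the bias is d × 0 = 0. The mean shift goes into the time effect, and a mixture of raters adds variance p(1 − p)d² to the follow-up scores.

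The protocol gives neither d, nor its sign, nor any p_k, so no value can be put in. This formula also leaves out the separate effect of knowing the arm, for which there is no figure either.

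**The case against.** The strongest reply is that this is a slip of wording about one secondary outcome, that an operations manual would settle it, and that no section says raters will in fact change. Part of that stands. The primary outcome is the Letter-Number-Span-Test, which this contradiction does not touch, and a switch of rater is something the text permits, not something it plans. But the article does not leave the rater to another document. It states the rater more than once, incompatibly, and one of the versions puts unmasked session supervisors in charge of an interview score.

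A reader might go further and infer any of the following. The document supports none of them.

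- **That the bias favours the gaming arms.** This needs RAs to score symptoms as milder than psychiatrists do. No section says so, and the opposite would reverse the sign.
- **That differing RA availability by arm would by itself produce support for hypothesis 3.** RAs attend the sessions of both gaming arms, so a different mix of raters is suggested at most for the contrast with treatment as usual. The hypothesis needs superiority over both comparators.
- **That the psychiatrists are the only raters who could be masked.** The psychologist has no stated gaming role either. Nor does the protocol say whether the psychiatrists belong to the unit staff who cannot be masked. No masked psychiatrist rating is promised anywhere.

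**Conclusion.** The contradiction is explicit and should be corrected. As written, CAINS may be rated at follow-up by a person who knows the allocation and supervised the participant's gaming, or by a different type of rater than at baseline. That is enough to weaken the reading of hypothesis 3 in either direction.

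The size and direction of any bias cannot be derived from the document. A change of rater type that is the same in all arms would mainly add noise. Bias needs either a rater mix that differs by arm or ratings influenced by knowledge of the arm, and the text excludes neither. The conclusion rests on the wording of the three sections and on CAINS being the only measure of negative symptoms. It rests on no assumed number. The matter is more than clerical, because the choice between the versions decides whether unmasked session supervisors rate this outcome, but it is confined to a secondary outcome.

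**What to change.** Reconcile the three sections:

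1. In the data-collection text after Table 1, remove negative symptoms from the outcomes that a psychologist or RA may collect.
2. In the outcome section, state that the trained psychiatrists already named there rate CAINS at baseline, 3 months and 6 months in all three arms, and that they are not told the allocation where this is feasible.
3. In the blinding section, except CAINS from the follow-up outcomes collected by RAs, and state the masking of the CAINS raters.
4. Record the rater at each visit, so that departures can be seen and described.

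The wording costs little. The practical cost is less flexible visit scheduling: with 234 participants (78 per arm in the Interventions section) and three visits, psychiatrists would conduct up to 234 × 3 = 702 interviews. The outcome section already commits the trial to psychiatrist rating, but the protocol does not say how many psychiatrists are available, so it cannot be assumed that no further staff time is needed. Keeping the same psychiatrist for each participant, or using one from outside the treating unit, would be a sensible preference but is not needed to resolve the contradiction.
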